### Para-clinical parameters

Postural balance will be measured by a clinical test (the BESS) and posturography.

1. The Balance Error Scoring System (BESS)

The BESS assesses static postural balance (eyes closed) in six conditions, using three positions (double leg stance *vs.* single leg stance *vs.* tandem stance) on two surfaces (firm *vs.* soft) (Figure 5). The participant must remain balanced without moving for 20 seconds. Points are given for postural errors (e.g., eye opening, hip flexion greater than 30°, etc.). The sum of the points obtained in the six conditions gives the total BESS score (Docherty et al., 2006)

 
[figure not shown]

**Figure 5 –** The Balance Error Scoring System is a clinical test that assesses static postural balance in six conditions, using three positions (double leg stance *vs.* single leg stance *vs.* tandem stance) on two surfaces (firm *vs.* soft).

1. Posturography

Posturography is the recording of static postural balance using a stabilometric platform (FEETEST 6^©^, Techno Concept^®^, France) (Figure 6). It consists of four small platforms that locate the position of the body’s center of pressure from the coordinates of four points of contact (left heel, left metatarsal, right heel and right metatarsal). Postural recording takes place with eyes closed, and lasts approximately one.

[figure not shown]

**Figure 6** – The FEETEST 6^©^ platform (Techno Concept^®^).

To ensure reproducibility in measurements of para-clinical parameters, investigators from the units involved in the initial assessment visit will be trained in how to carry out the BESS test (using a video). Similarly, a standard procedure will be put in place for posturography measurements.

1. Psychometric data

Self-report questionnaires will be used to measure postural awareness (the Postural Awareness Scale) and perceived stress (Cohen’s Perceived Stress Scale).

- 1. The Postural Awareness Scale (Cramer, Mehling, Saha, Dobos, & Lauche, 2018)

This questionnaire evaluates body awareness involved in postural control. A French version is currently being validated. The questionnaire is made up of 12 items, each rated from 1 (not at all true about me) to 7 (very true about me). The questionnaire assesses two dimensions of postural awareness: (*i*) Ease/Familiarity with Postural Awareness; and (*ii*) Need for Attention Regulation with Postural Awareness.

- 1. Cohen’s Perceived Stress Scale (Cohen, Kamarck, & Mermelstein, 1983)

This questionnaire evaluates how individuals rate their perception of stress. It consists of 14 items, each rated from 1 (never) to 5 (often). A high score on the questionnaire indicates a high level of perceived stress.

The two questionnaires are presented in APPENDIX 3. Participants will complete paper-based versions.

### Biological parameters

A saliva sample will be collected during the initial evaluation visit, and the end-of-study visit (2 x 2 ml at each visit). These samples will be used to monitor markers of the corticotropic axis (cortisol and DHEA), and the autonomic nervous system (alpha-amylase and chromogranin).

## Data collection methods

A paper-based Case Report Form will be created for the study.

The person(s) responsible for maintaining Case Report Forms must be clearly identified in the task allocation document. Each Case Report Form will be strictly anonymous and labelled using the participant’s identification number. During the study, or when it ends, the data collected and transmitted to the sponsor by the persons directing and supervising the research (or any other specialist) will be anonymized. Under no circumstances can the names or addresses of the persons concerned appear in clear text.

## Data flow

Clinical data will be recorded in a database, consistent with the data recorded in the paper-based Case Report Form.

All data recorded in the Case Report Form and *via* questionnaires will be entered by optical reading of paper-based documents (OMR Manager software), and inconsistent data will be checked manually. These data, together with data from various salivary assays, will be consolidated in an anonymized database held on a secure computer with up-to-date security software. Regular back-ups will be made on secure removable media. This medium will be regularly checked for viruses.

Access to this data will be restricted to authorized persons (investigators and collaborators).

The physical security of all materials will be ensured by keeping them in locked premises on a guarded military compound.

## Data access and confidentiality

The sponsor is responsible for obtaining the agreement of all parties involved in the study in order to guarantee direct access to all study locations, source data, source documents and reports needed for quality control and audit purposes.

The persons directing and supervising the study will make any documents and individual data that are essential for monitoring, quality control and auditing the study available to persons authorized to access these documents in accordance with the legislative and regulatory provisions in force.

In accordance with current legislation, in particular Articles L.1121-3 and R.5121-13 of the French Public Health Code, persons with direct access to source data (for example, investigators, quality control personnel, instructors, clinical research assistants, auditors and any other persons called upon to collaborate in the trials) will take all necessary precautions to ensure the confidentiality of information relating to the study, and those who participate, notably their identity, and the results obtained. These persons, together with those directing and supervising the study, are bound by the conditions of physician–patient privilege.

During, or at the end of the study, individual data that is collected and reported to the sponsor by the persons directing and supervising the study (or any other specialized parties) will be codified. Under no circumstances should the names or addresses of the persons concerned appear in plain text.

Participants will be coded as follows: unit code (GIGN – GI, CPA 10 – CP, 1^ier^ RPIMA –RP, 13^ième^ RDP –RD, ECOFUS – EC, BSPP – BS); a number indicating the order of inclusion in the unit; the first letter of the participant’s surname and first name.

The sponsor will ensure that each person involved in the study has been informed about access to personal data, which is essential for quality control purposes.

# STATISTICAL ASPECTS

## Calculating the number of subjects required

To date, there are no data in the literature on the effectiveness of POTs in preventing sports-related injuries. However, discussions with military unit managers and medical officers suggest that a reduction in the injury rate of around 15% would be clinically relevant. Preliminary epidemiological data from the various units indicates that the rate of fall injuries is around 50%.

To determine the sample size required to observe a significant difference in rates between the two groups, we used the following parameters:

- statistical test: two-tailed
- fall rate in the active control group: 50%
- fall rate in the POTs group: 35%
- statistical significance = 0.05
- power = 0.80

Taking into account potential drop-outs (estimated at 10%), the sample should consist of 200 participants per group, for a total of 400 participants over the two years of the study.

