| Objectives | The main objective is to evaluate the effectiveness of POTs in preventing fall injuries during physical activities in the military context.  Secondary objectives:  The first secondary objective is to test the mechanistic hypothesis that POTs can reduce the risk of fall injury by improving postural awareness.  The second secondary objective is to test the mechanistic hypothesis that POTs can reduce the risk of fall injury by decreasing the intensity of the psychobiological stress response during physical activities in the military context.  The third secondary objective is to use machine learning to develop a predictive model of the risk of fall injury, based on clinical (the BESS test) and paraclinical (posturography) measurements taken prior to the start of physical activities in the military context.  The fourth secondary objective is to evaluate the persistence over time of the effectiveness of a POT intervention in preventing the risk of fall-related injury. The rate of fall injuries will be compared for POTs and active control groups among participants who continue to engage in physical activities after the end-of-study visit (and complete the selection course). |
| Research outline | This is an open, prospective, controlled, single-center cohort study. |

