# SCIENTIFIC JUSTIFICATION

## Current knowledge

### Pathology/ health problems and current knowledge

Physical activity and sport play an important role in the military, as they are used to develop and optimize the operational capacity of combatants. In France, *Entraînement Physique Militaire et Sportif* (Physical and Sport Training for the Military) is designed to enable all military personnel to acquire the physical and mental capacities they need to perform their duties (Etat-major des armées - Centre national des sports de la défense, 2011). In addition, the preservation of operational capacity throughout a military career is based, among other things, on the health benefits of sporting activities, notably with respect to the prevention of chronic, stress-related pathologies such as cardiovascular disease and depression (World Health Organization, 2003).

Nevertheless, physical activity and sport can also be the source of acute (sprains, fractures, etc.) and chronic (tendinopathies) musculoskeletal pathologies. In particular, there is a high rate of lower-limb trauma during physical activities in the military context, both among young enlisted personnel [15–20%] (At, 2016; Bauvent, 2014; Pleche, 2018) in operational military units or during selection courses for specialized units [30–45%] (Bertrand, 2016; Brocard, 2014; Chipault, 2016; Longin, 2015; Morinière, 2013). In addition to their impact on the health of combatants, these injuries have a negative impact on the operational capability of forces (due to incapacity) and a significant economic cost (Ressort, Desjeux, Marsan, & Thevenin-Garron, 2013)

Identifying risk factors is an essential step in developing an injury prevention strategy. Classically, there are two categories of risk factors: (*i*) those that are intrinsic to the individual, and include age, gender, physical condition or tobacco consumption; and (*ii*) extrinsic factors, which relate to the context in which the sporting activity is performed, and which include environmental conditions (temperature, humidity, etc.), the type of activity, or training conditions (progression, regularity, etc.). (Bigard, Cravic, & Banzet, 2010; Meeuwisse, 1994; Williams, 1971). The identification of modifiable risk factors (i.e. those that are amenable to an intervention that will reduce the likelihood of injury), remains a major challenge in the field of sport (Bahr & Holme, 2003).

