## Study outline

In order to guarantee compliance with the experimental protocol over the two years of the study (see paragraph 3.3 for a detailed explanation), the active control intervention will be carried out in the first year (year Y), while the POTs intervention will be carried out in the second year (year Y+1).

The study will be carried out in the following six units the in the French armed forces :

1. the National Gendarmerie (Versailles-Satory, 78)
2. the 10th Air Parachute Commando (Orléans, 45)
3. the 1st Marine Infantry Parachute Regiment (Bayonne, 64)
4. the 13th Parachute Dragoon Regiment (Souge, 33)
5. the Paris Fire Brigade (Villeneuve-Saint-Georges, 94)
6. the Fusiliers Marins [Navy Riflemen] School (Lorient, 56)

The study will take place during the selection courses organized by each unit, and will last three weeks.

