# ELIGIBILITY CRITERIA

## Recruitment procedures

Participants will be volunteers recruited from among candidates for the selection course organized by the various units. They will be in good health and physical condition, as they will have been declared medically fit to enroll in the course. Participation in the study will be open to all candidates who qualify for the selection course.

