## Data collected

### Clinical parameters

Clinical data collection will be limited to injury history, age, sex, height and weight. These data will be recorded using posturography software.

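### The primary comparison pools six units across two years and gives unit no role, so a change in unit mix between the years would bias the estimated POTs effect

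*Protocol*

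**What the plan says.** The Protocol's Study outline section names six units in different towns, each running its own selection course, and fixes one order for all of them: "the active control intervention will be carried out in the first year (year Y), while the POTs intervention will be carried out in the second" (meaning Y+1). The Randomization section confirms that this order does not vary between units. Treatment group and calendar year therefore coincide in every unit.

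Enrolment is planned only in total. The section Calculating the number of subjects required says "the sample should consist of 200 participants per group, for a total of 400 participants over the two years of the study". Recruitment procedures gives no number or share per unit: "Participation in the study will be open to all candidates who qualify for the selection course".

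The primary analysis, under Statistical methods, is a Cox model with clinical variables as potential confounders plus a log-rank comparison of the two groups. No stratification is stated. The Clinical parameters section says which clinical variables exist: "Clinical data collection will be limited to injury history, age, sex, height and weight". Unit is not among them, although the Data access and confidentiality section builds a unit code into each participant identifier.

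The Research Summary describes the design differently: "This is an open, prospective, controlled, single-center cohort study". That cannot be reconciled with six units at six locations.

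**The concern.** Each unit's control-year intake is the natural comparator for its own POTs-year intake, but the stated analysis compares one pooled year with another. Such a comparison is free of unit effects only if the units contribute in the same proportions both years, or if their injury risks are equal. The Protocol secures neither.

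Different risks are plausible on the Protocol's own reasoning. Its introduction lists environment, type of activity and training conditions among the extrinsic risk factors for injury, and notes that one obstacle challenge was the leading source of trauma on the marine commando course. These are properties of a course, and so of a unit, whereas the named confounders describe only the individual.

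If higher-risk units supply a smaller share of year Y+1 than of year Y, the pooled injury rate falls with no effect of POTs. The opposite shift hides a real effect.

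**Working it through.** **The plan's own figure.** Inputs from the sample-size section: control rate 50%, POTs rate 35%, power 0.80, 10% drop-out, "statistical significance = 0.05", "statistical test: two-tailed".

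- Two-proportion formula: n = [1.96·√(2·0.425·0.575) + 0.842·√(0.25 + 0.2275)]² / 0.15² = 170 per group, or 183 with continuity correction.
- Drop-out: 183/0.9 = 204 (183 × 1.1 = 202). Without the correction, 170/0.9 = 189.

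The stated 200 is therefore sound. It leaves 200 × 0.9 = 180 evaluable per group, with power of about 82%. The problem is not the total but the absence of unit from the comparison.

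**Bias from a shift in mix.** Group the units into a lower-risk and a higher-risk set.

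Spurious difference = (higher rate − lower rate) × (change in the higher-risk share).

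The Protocol gives no unit rates, so the rates below are assumptions centred on its 50%, with half of the control year coming from higher-risk units. Error rates use the pooled two-proportion z-test at 180 per group as an approximation to the log-rank test.

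No true effect, higher-risk share falls in year Y+1:

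| Assumed unit rates | Shift in share | Spurious difference | Type I error |
| --- | --- | --- | --- |
| equal | any | 0 | 5% |
| 45% / 55% | 10 points | 0.10 × 0.10 = 1 point | 5.4% |
| 40% / 60% | 10 points | 0.20 × 0.10 = 2 points | 6.7% |
| 40% / 60% | 20 points | 0.20 × 0.20 = 4 points | 11.8% |
| 30% / 70% | 20 points | 0.40 × 0.20 = 8 points | 33% |

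For the fourth row: control 0.5 × 60 + 0.5 × 40 = 50%; POTs year 0.3 × 60 + 0.7 × 40 = 46%.

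True 30% relative reduction in every unit, higher-risk share rises by 20 points (40% / 60%): POTs-year rate 0.7 × (0.7 × 60 + 0.3 × 40) = 37.8%, observed difference 12.2 points, power about 65% against 82% with no shift.

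**A unit that enrols in one year only.** Suppose six equal units average 50% and one at 70% leaves after year Y. The other five average (6 × 50 − 70)/5 = 46%, again a spurious 4 points.

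**Creating the whole 15-point target effect** needs gap × shift = 0.15, for example a 50-point gap with a 30-point shift. That is far beyond anything the Protocol suggests.

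**The case against.** **The plan keeps the units together.** The same six units are named for both years, the same schedule applies each year, and the control sessions are supervised by the person who will run POTs in that unit the following year. Each unit is thus meant to serve both arms. This stands: mix can change only through unequal recruitment or a unit dropping out. Neither is improbable over two annual intakes of volunteers, and the analysis has no protection against either.

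**The covariate list may belong in the analysis plan.** Detailed covariates and stratification factors are often left to an SAP, which is not shown here, and the sentence limiting clinical data is about collection rather than model terms. This has some force: unit is recorded, so an SAP could use it. But the Protocol does name its class of confounders, and unit falls outside it.

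**Stronger readings.** A reader might infer from the introduction that the six units have very different injury risks, since it gives 15–20% for young enlisted personnel and 30–45% for operational units or specialized selection courses. The documents do not support that. Those ranges concern lower-limb trauma rather than fall injury. They contrast other populations, and all six study units run selection courses, so the lower band is not shown to apply to any of them. Nor can rates of 45% or less average the planned 50%. A reader might also infer that recruitment simply continues until 200 per year is reached. The Protocol states a target, not that rule.

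**Conclusion.** The point holds as a weakness of the stated primary analysis. Group equals year, enrolment is fixed only in total, and unit has no stated role in either the Cox model or the log-rank test, so a change in unit mix would bias the comparison in either direction.

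The size is not known. It rests on two assumptions the Protocol cannot settle: how far unit risks differ, and how far unit shares move. With modest values the bias is minor (about 1 point). With a 20-point risk gap and a 20-point shift it reaches 4 points, just over a quarter of the 15-point target (4/15 = 27%), and the type I error more than doubles. With equal unit risks, or constant shares, it is zero. The planned 200 per group is not in question.

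**What to change.** - In Statistical methods (main objective) and the matching Research Summary entry, stratify the primary Cox model and log-rank test by unit, so that each unit's POTs year is compared with its own control year.
- Report enrolment by unit and year.
- In the Research Summary, replace the single-center description with six units.

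**Cost.** Protocol wording only. Unit is already in the participant code and 200 per group stands. At the planned rates about 180 × 0.50 + 180 × 0.35 = 153 events are expected, about 25 per unit on average, so six strata are affordable. A unit that enrols in one year only adds nothing to the stratified contrast. With six equal units, losing one leaves 5/6 of the information and raises the standard error by about 10% (√1.2 = 1.095).

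Enrolment quotas matched by unit are not needed and would sit badly with recruitment open to all qualifying candidates. A separate rule excluding one-year units is redundant once the analysis is stratified. Stratification deals with unit mix only: confounding of intervention with calendar year remains and should be acknowledged separately.

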## Randomization

There will be no randomization (POTs versus active control) at the individual level (i.e., for each participant in each military unit). This is not possible due to the risk of participants in the POTs group influencing those in the active control group (contamination bias). The conditions under which the selection course is carried out mean that participants in both groups are in close contact with each other. Moreover, it is possible that running the two interventions at the same time may undermine the desired team cohesion. Hence, we have chosen to carry out the study over two successive years (years Y and Y+1):

1. Participants included in year Y will follow the active control program.
2. Participants included in year Y+1 will follow the POTs program.

The order of the two interventions (active control followed by POTs) is deliberately not randomized between units, to ensure that the research protocol is respected throughout the study. If the POTs intervention was run in year Y, and was found to be beneficial, it would be very difficult to expect participating units to set up an active control in year Y+1, as it is unrealistic to expect them to abandon a program with potential benefits for candidates.

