**Analysis of the main objective**

The effect of the intervention (POTs *vs.* active control) on the rate of fall injuries will be evaluated using a comparative survival analysis (the Cox model, with clinical variables as potential confounders). Survival curves for POTs and active control groups will be compared using the log-rank test.

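### Treatment is assigned to whole unit-years, but the sample size and primary analysis treat participants as independent, so 0.80 power and 5% error hold only if a unit's injury rate does not vary between its two yearly intakes

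*Protocol*

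**What the plan says.** On design, the Study outline section states "The study will be carried out in the following six units" and places the active control in year Y and POTs in year Y+1. The Randomization section adds "There will be no randomization (POTs versus active control) at the individual level". It gives contamination and team cohesion as reasons, and it keeps the same order in every unit on purpose. Treatment is therefore set for 12 unit-years, six per arm.

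On sample size, the section on calculating the number of subjects uses fall-injury rates of 50% and 35%, "statistical test: two-tailed", "statistical significance = 0.05", power 0.80 and 10% drop-out, and concludes that "the sample should consist of 200 participants per group, for a total of 400 participants over the two years of the study". No ICC, design effect or number of clusters appears.

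On analysis, the main objective is addressed by a Cox model with clinical variables as potential confounders, and "Survival curves for POTs and active control groups will be compared using the log-rank test". The Clinical parameters section limits the clinical data to injury history, age, sex, height and weight, so unit is not among them. The Research Summary describes the design thus: "This is an open, prospective, controlled, single-center cohort study".

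**The concern.** Participants in one unit-year have much in common. Each unit has one designated instructor, sessions are given in groups, and the medic in charge of care on the course records the endpoint. The Randomization section itself rejects individual allocation because candidates are in close contact and would influence each other. For the marine commando course, the Scientific Justification describes challenges at height in all weathers, and such conditions can plausibly differ between two intakes.

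If a unit's injury rate shifts from one year to the next for such reasons, the shift falls wholly into the treatment contrast. An analysis that counts 400 independent people attaches no variance to it. The confidence interval is then too narrow, a null effect is rejected too often, and the trial has less power at a true 5% level than stated.

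**Working it through.** **Reproducing the Protocol's figure.** Inputs: p1 = 0.50, p2 = 0.35, two-sided 0.05, power 0.80, drop-out 10%. With the pooled-variance formula:

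n = [1.96·√(2·0.425·0.575) + 0.8416·√(0.25 + 0.2275)]² / 0.15² = 169.3, so 170 per arm.

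The continuity correction gives 183. Drop-out then gives 183/0.9 = 204, or 183 × 1.1 = 202. The stated 200 is reproduced to within 3% and is an individual-level figure. With 200 × 0.9 = 180 analysed per arm, power without continuity correction is Φ[(0.15·√180 − 1.96·0.6991)/0.6910] = 0.82.

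**Adding unit-year variation.** Assumptions, none of them in the Protocol: equal intakes, so 180/6 = 30 analysed per unit-year, and an extra ICC of 0.01 to 0.05 between years within a unit. At a 50% rate the unit-year SD is √(0.25·ICC).

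- Design effect: DE = 1 + (m − 1)·ICC.
- Power at a true 5% level: the formula above with 180/DE in place of 180.
- Type I error of the unadjusted test: 2·[1 − Φ(1.96/√DE)].
- Six-pair t analysis: noncentral t, 5 df, noncentrality 0.15/√(0.4775·DE/180).

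The last three columns repeat the calculation for independent clusters of 15, as if each unit ran two courses a year with unrelated course effects.

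| ICC | SD (points) | DE, m = 30 | Power | Type I | Six-pair t power | DE, m = 15 | Power | Type I |
|---|---|---|---|---|---|---|---|---|
| 0 | 0 | 1.00 | 0.82 | 5.0% | 0.65 | 1.00 | 0.82 | 5.0% |
| 0.01 | 5.0 | 1.29 | 0.72 | 8.4% | 0.54 | 1.14 | 0.77 | 6.6% |
| 0.02 | 7.1 | 1.58 | 0.63 | 11.9% | 0.47 | 1.28 | 0.72 | 8.3% |
| 0.05 | 11.2 | 2.45 | 0.45 | 21.1% | 0.33 | 1.70 | 0.60 | 13.3% |

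These are two-proportion results, used as a proxy for the log-rank test and Cox model.

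**Simulation of six units over two years (30 per unit-year).**

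- The unadjusted test rejected a true null in 8.6%, 12.1% and 21.3% of trials at ICC 0.01, 0.02 and 0.05. The six-pair t test stayed at about 5%.
- With stable unit differences only (unit ICC 0.05 or 0.10), the unadjusted test rejected in 4.6% and 4.2%.
- A unit-stratified test without a unit-year term still rejected in 8.0%, 10.9% and 20%.
- A linear analogue of a unit-stratified model with a unit-year random effect, referred to the normal distribution, rejected in about 5.5%, 7.3% and 9.3%.

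**Could more participants restore 0.80?** With six unit-years per arm, the analysed number needed is 170·(1 − ICC)/(1 − 170·ICC/6). Divided by 0.9, this is about 261 enrolled per arm at ICC 0.01 and 427 at 0.02. Above ICC = 6/170 = 0.035 no number suffices.

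**Year effect common to all units.** If the overall rate varied with an SD of 5 points per year (assumed), the variance of the contrast would be 2·0.05² + 2·0.25/180 = 0.00778 instead of 0.00278, a ratio of 2.8. The false-positive rate would be 2·[1 − Φ(1.96/√2.8)] = 24%, and no cluster adjustment would change that.

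**The case against.** Several points on the other side have weight.

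- **The size depends on an assumed ICC.** At ICC 0 the stated power and error rate hold. A reader might infer that they simply fail; the Protocol does not support so flat a statement.
- **Stable unit differences are not the problem.** A reader might infer that six different units by themselves invalidate the 5% level. Every unit contributes to both arms, so with balanced intakes these differences largely cancel, and the simulation shows a slightly conservative test.
- **Clusters may be smaller than 30.** The Protocol gives neither unit sizes nor courses per unit per year, and Appendix 2 caps session groups at 20 to 25. Clusters of 15 give clearly milder figures, though still not the stated ones.
- **The analysis section is silent rather than exclusive.** A statistical analysis plan that is not shown could add strata, a frailty term or robust variance. That stands for the model. It does not rescue the sample-size section, where 0.80 is fixed on an independence assumption.
- **Part of the power loss under the six-pair t test is the price of 5 df.** That test has about 0.65 at ICC 0, so the whole drop from 0.82 must not be put down to clustering.

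**Conclusion.** The point holds in conditional form. The arithmetic behind 200 per group is right for independent participants, but the design does not assign treatment to independent participants. The claims of 0.80 power and 5% error rest on there being no year-to-year variation in injury rates within units, an assumption that is neither stated nor supported. An ICC of only 0.01, which is a 5-point SD in a unit's yearly rate, already takes power to about 0.72 and type I error to about 8% with clusters of 30 (0.77 and about 7% with clusters of 15). At ICC 0.05 the figures are 0.45 and 21% (0.60 and 13%). They assume equal intakes, 180 evaluable per arm and a two-proportion proxy.

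A reader might also infer that stratifying by unit, or adding a unit-year frailty, settles the matter. Stratification alone leaves the within-unit year variation in place, and a random-effect analysis with a normal reference did not restore 5% in the simple analogue. Confounding with calendar year is a separate limit that no such model removes. The single-center label, set against six named units, is a secondary wording correction.

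**What to change.** Keep 400 participants and change the statistical text:

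1. **Sample-size section.** Replace the single power of 0.80 with power over a stated unit-year ICC range, for the analysis that will be used. For the six-pair t analysis that is about 0.65 at ICC 0 and 0.54, 0.47 and 0.33 at 0.01, 0.02 and 0.05. State the expected intake and number of courses per unit per year.
2. **Analysis of the main objective.** Take the primary confidence interval and p-value at unit-year level with a small-sample reference, for example the paired analysis of the six within-unit differences between year Y and year Y+1 (t, 5 df). A unit-stratified Cox model with a unit-year frailty may be reported alongside, but not as the primary test with a normal reference. The unit code is already part of each participant code.
3. **Interpretation.** State that the contrast estimates POTs plus any year effect common to all units. Where the units' existing injury data cover more than one earlier year, use them to show how large such swings are.
4. **Research Summary.** Correct the single-center description.

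The cost is a wider interval and a less favourable stated power. No new participants or trial measurements are needed.
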